### Training Protocol

Subjects will perform HIIT or moderate CAE on a stationary bicycle (Lode Corival, Lode Inc.) 3×/week for two periods of 4 weeks in a group of four subjects (Figure 1). The order of the intervention phases will be randomized. Training will take place on Mondays, Wednesdays, and Fridays, to allow for sufficient recovery periods between training sessions.

**Figure 1 F1:**
[figure not shown]
Intensity-work rate plot for CAE and HIIT session. **Left:** intensity-work rate plot for a 50-min CAE intervention session. **Right:** intensity-work rate plot for a 30-min HIIT intervention session. CAE training intensity will be at about 55% W-max, HIIT will alternate between training intensity 35% W-max during low-intensity intervals and >85% W-max at high-intensity intervals. CAE, continuous aerobic exercise; HIIT, high-intensity interval training.

Each HIIT session is about 30 min of interval training, starting with a 5 min of warm-up at 25–35% W-max. Subsequently, six to eight blocks of HIIT will be performed, alternating 45 s at >85% VO_2_-max, with 90 s at 30–40% W-max. After the interval block, 5 min of cooling-down will be performed at 20–35% W-max. Workload will be progressively adapted using a fixed weekly schedule or upon therapist decision by adding intervals at the end of the sessions.

Each CAE session is about 50 min of continuous training at a preset workload of about 55% W-max. Workload will be progressively adapted after every week by reducing rest time, based on a fixed schedule or upon therapist decision. A trained physiotherapist-supervisor, assisted by GCP-trained interns from the Faculty of Human Movement Sciences will assist the subjects with water, music, and motivational encouragements. Throughout the study, patients are asked to maintain their regular medication.

The Ecological Momentary Assessments taken weekly (A phases) or every other day (B/C phases) using the online survey throughout the study period will act automatically as reminders and will help with compliance to training and assessments. We will comply with consensus recommendations of Slade et al. (47) regarding reporting on exercise interventions.

### Statistical Analysis

Although the protocol specifies primary and secondary study outcomes, we will assess the results based on a combination of those parameters.

For example, the primary research parameter that we have specified is the MDS-UPDRS-III, which is measured before and after each phase. If, under the influence of the interventions, there are improvements within the participants that are greater than the measurement error of 3.25 points known from the literature (48), this is a clear indication that the intervention influences motor function. However, if there is less or no change in the MDS-UPDRS-III but in one or more other parameters, this is still informative with regard to the effects of the different interventions and the underlying mechanisms. If no change is visible in any parameter under the influence of the interventions in any participant (through visual analysis and/or statistical tests), then the conclusion should be that there is no effect.

Visual inspection is the method of choice for single-subject research designs (SSRDs) (24). We will inspect, analyze, and describe the changes across the baseline and intervention phases (phase mean level and data spread), and we will compare the trend (slope) of scores with the baseline mean levels and variability (standard deviations) on outcomes for each intervention strategy and each patient. Longitudinal regression analysis with “phase” (i.e., condition) as the independent variable will be used for further confirmation (α = 0.05).

We will not explicitly test for group differences between patients in Hoehn–Yahr stage 1–2 or for patients in Hoehn–Yahr stage 2.5–3, but we will get insights on the direction of effects and effect sizes in the intervention phases compared with the baseline phases, which we will report descriptively for both participants in both subgroups.

The association between biomarkers and symptom changes will be quantified by Pearson correlation coefficients and corrected for age, between changes in BDNF, α-synuclein, and Nfl and change scores on primary and secondary parameters.

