## Methods

### Study Design

We will use a single-subject alternating treatment approach with A1-B-A2-C-A3 or A1-C-A2-B-A3 design to study the effects of HIIT on motor and non-motor performance and neuroplasticity and neurodegeneration biomarkers such that subjects will perform both the HIIT (B-phase) and the moderate CAE training (C-phase) for 4 weeks. After a baseline (A1) period of 4 weeks, the first intervention period of 4 weeks will take place (B or C), followed by a washout period of 8 weeks without an intervention (A2), the second intervention period of 4 weeks (B or C), and finally a third washout period of 8 weeks (A3). Each patient therefore experiences the full set of treatment approaches. The order of interventions B and C will be randomized for each participant (i.e., ABACA or ACABA, two of each, four participants total) using a random sequence generator. Assessment will be done by Good Clinical Practice (GCP)-trained blinded assessors.

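### The stated rule rarely allows a negative verdict, and when it does it concludes absence of effect from four people

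*Protocol article*

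**What the plan says.** Under Outcome Measures the article names one primary parameter, MDS-UPDRS-III. The Statistical Analysis section then says that, despite the primary and secondary labels, "we will assess the results based on a combination of those parameters". It does not define the combination.

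Three cases follow:

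- A within-participant MDS-UPDRS-III improvement larger than a measurement error of 3.25 points is taken as a clear sign of influence on motor function.
- If MDS-UPDRS-III changes less or not at all, but there is a change "in one or more other parameters, this is still informative with regard to the effects of the different interventions" and the mechanisms behind them. No threshold is set for these other parameters.
- "If no change is visible in any parameter under the influence of the interventions in any participant", judged by visual analysis and/or statistical tests, "then the conclusion should be that there is no effect".

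Visual inspection is the main method. Longitudinal regression on phase, at α = 0.05, is added as confirmation. The Study Design section gives "ABACA or ACABA, two of each, four participants total", each receiving both HIIT and CAE.

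**The concern.** The third case is the only route to a negative conclusion, and it requires silence from every outcome in every participant. With many outcomes, four people and two interventions, some visible or nominally significant change is likely from noise alone. The rule then has little ability to return a null when there is nothing to find.

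If the null is reached, the wording turns absence of visible change into a statement that no effect exists. Four participants and sparse measurement of the primary outcome cannot carry that statement.

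The rule also asks only whether something changed under the interventions. The central hypothesis in the Introduction is that HIIT is better than CAE, so a change somewhere need not bear on it. The Discussion says the results are meant to help future well-powered trials. A near-automatic signal or an unsupported statement of no effect would be a poor basis for designing them.

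**Working it through.** The article gives no error rate or power figure for this rule, so there is none to reproduce.

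**Inputs**
- Outcomes measured at least weekly during training (Table 1 and Outcome Measures): 10-m walk, one-leg stance, three VAS scores, three biomarkers and the activity tracker, so 2 + 3 + 3 + 1 = 9. TUG is described as weekly in the text, but Table 1 shows it once per intervention phase, so it is left out.
- Participants: 4. Interventions: 2. α = 0.05 per test (two-sided assumed; sidedness is not stated).

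**Chance of at least one result when nothing has an effect**

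With m independent comparisons this is 1 − 0.95^m.
- One intervention: m = 9 × 4 = 36; 1 − 0.95^36 = 1 − 0.158 = 0.84.
- Both interventions: m = 72; 1 − 0.95^72 = 1 − 0.025 = 0.975.

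**Correlated outcomes**

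Let the nine test statistics within a participant share a common correlation r, with participants independent and the two interventions treated as independent. If p is the chance of at least one result among the nine, the study-level chance is 1 − (1 − p)^4 for one intervention and 1 − (1 − p)^8 for both. Values of p come from numerical integration of a one-factor normal model. The values of r are assumptions.

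| r | p | one intervention | both |
|---|---|---|---|
| 0 | 0.370 | 0.84 | 0.975 |
| 0.3 | 0.326 | 0.79 | 0.96 |
| 0.5 | 0.269 | 0.71 | 0.92 |
| 0.7 | 0.202 | 0.60 | 0.84 |
| 0.9 | 0.124 | 0.41 | 0.65 |

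**Improvements only**

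At 0.025 each and independent: 1 − 0.975^36 = 0.60 and 1 − 0.975^72 = 0.84.

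Two features are not in these figures. Serial correlation raises the error of a naive comparison of four with four observations from 0.05 to about 0.11 at an AR(1) coefficient of 0.3, and to 0.18 at 0.5. Visual inspection used as an alternative route to a change would raise the totals. Used jointly with a test it would lower them.

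**What a null can support**
- No responder among four: solving (1 − p)^4 = 0.05 gives p = 1 − 0.05^(1/4) = 0.527. A true responder share of up to about 53% is not excluded (one-sided 95%), even if every responder would be recognised.
- MDS-UPDRS in Table 1: once at the start of A1, of the first intervention, of A2, of the second intervention and of A3, and once at the end of A3. That is six visits over five phases, so 6 − 5 = 1 residual degree of freedom per participant. Power for a 2-SD shift between two single visits (noncentrality 2/√2 = 1.41) is about 0.09. Pooling the four A-phase visits gives 3 degrees of freedom, noncentrality 2/√(1 + 1/4) = 1.79 and power of about 0.24.
- A weekly outcome with four observations against four (6 degrees of freedom, noncentrality √2 = 1.41 for a 1-SD shift): power of about 0.22.

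**The case against.** The text does not say that any change in any outcome is an effect. It grades the evidence: a primary change above 3.25 points is a clear indication, and other changes are only informative. A reader might infer that whatever is not a null is a positive verdict. The documents do not state that, so the figures above are the chance that the null is blocked, not the chance that the authors will declare efficacy. This stands.

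A reader might also multiply all 22 listed outcomes by four participants and two interventions to reach 176 tests and a chance of 99.99%. Table 1 does not support that count. MoCA is taken three times in all, MDS-UPDRS six times over five phases, and TUG once per intervention phase. The article also does not say whether regressions are run per participant or pooled. Hence the restriction to nine outcomes, which is itself an assumption about how the analysis will be run.

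The study is declared an exploratory pilot, visual inspection is a recognised primary method for single-subject designs, and family-wise error is a debatable yardstick here. Multiplicity detail may also sit in an analysis plan that is not shown. This lowers the severity. It does not rescue the rule, because the problem is what the article states: an exploratory study can report estimates without a verdict, but this one prescribes a verdict of no effect.

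Finally, if the null is seldom reached, its wording seldom does harm. That is fair as to frequency, but the inference is still invalid when it is made.

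**Conclusion.** The point holds as a fault in the stated rule. The primary ranking gives way to an undefined combination, and the sole negative condition would usually fail under no true effect: 0.84 to 0.975 for nine well-measured outcomes if independent, and 0.71 to 0.92 at a correlation of 0.5. Only at an extreme correlation of 0.9 does the one-intervention figure drop below one half, to 0.41. These figures assume separate per-participant tests at two-sided 0.05 and leave visual judgement out.

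The null conclusion is unsupported whatever the count. Four people without a responder leave a responder share of up to about 53% open, and the primary outcome has one residual degree of freedom per participant when the five phases are modelled separately.

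It does not follow that the trial will claim an effect from any stray signal, or that all conclusions must rest on a single MDS-UPDRS-III contrast. That outcome is among the sparsest here, and such a restriction would give up much of what the frequent measurement is for. Severity: should be fixed.

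**What to change.** Two changes in the Statistical Analysis section:

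1. Replace the conclusion that there is no effect with a statement that no effect was detected, reported with intervals that show which effects remain possible.
2. Keep MDS-UPDRS-III as the named primary. State that changes in the other outcomes are hypothesis-generating, will be reported as per-participant HIIT-versus-CAE estimates with intervals (or with a false-discovery-rate adjustment if tests are reported), and do not by themselves support a conclusion of effect.

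The cost is a few sentences, with no added visits, participants or data. The real downside is that secondary signals, including the biomarkers, can no longer be claimed as effects. In a four-person exploratory pilot that loses little.

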## Discussion

Accumulating scientific evidence supports the use of physical rehabilitation training and exercise as an effective non-pharmacologic therapy to improve motor symptoms, problems with mobility and gait (49, 50), and non-motor features, including mood, cognition, and sleep [for review, see Reynolds et al. (51)] for patients at all stages of PD. Intensive exercise may even induce neuroplastic disease-attenuating effects via endogenous production of neurotrophic factors, including BDNF (4, 5, 52, 53).

There has been considerable progress in the area of physical training-induced neuroplasticity effects in PD (11, 54, 55), though our understanding is far from complete. Studies reported that PD patient show increased serum NfL protein levels (17) compared to age-matched healthy controls. NfL is a marker for axonal damage and related to cortical degeneration in PD (15). As we have stated earlier, the effect of physical exercise training on NfL serum protein levels in early or late stage PD is currently unknown.

Neurotrophic factors, including BDNF, are soluble endogenously produced polypeptides that are involved in the development, growth, functioning, and regulation of neurons and neuron-supporting cells. Studies indicate that continuous high-intensity training, moderate-intensity CAE, or low-intensity exercise enhances serum and plasma BDNF levels (12, 22, 52, 56). A recent meta-analysis showed cumulative evidence of physical exercise induced improved serum BDNF protein levels in PD (11). It is plausible that besides activation of the neurotrophic pathway (10), physical training increases blood flux into basal ganglia (57) and that this increased flux may stimulate vascular endothelial cells to secrete BDNF as a response to blood shear stress in the vessels (58). BDNF also has known cytoprotective effects on the striatum (59).

Reduced aerobic and anaerobic capacity are common in the elderly and especially in PD patients, though the rate of capacity reduction can be decreased by adopting a more active physical lifestyle (1). The experimental intervention in this study, HIIT, has already been used in sports science to improve both aerobic and anaerobic capacity (18); and preliminary studies are emerging in the field of PD. It is plausible that HIIT can be a time-efficient type of exercise that integrates both aerobic and anaerobic exercise, thereby enhancing the motivation of PD patients to comply with the intervention and in the long run promote a more active lifestyle. To our knowledge, we are the first to explore the within-subjects responses of blood biomarkers with weekly repeated measurements over multiple weeks (during baseline, washout, and intervention periods) for the two different exercise conditions. The design of the study allows for careful individual exploration of the response patterns of different exercise strategies on both symptoms and biomarkers. The advantage is that a small sample is enough to get important new knowledge, which will facilitate future well-powered clinical trials.

This study primarily explores whether HIIT is more effective at improving motor and cognitive performance than moderate CAE. If our hypothesis that HIIT is more effective than moderate CAE is correct, future HIIT studies in PD patients can add other treatment types, such as cognitive stimulation. For example, the Park-in-Shape study (60) investigated the feasibility of adding “exergaming” elements to improve adherence. Furthermore, a recent publication of a large observational study in PD patients in the Netherlands highlights the cost-effectiveness of specialized goal-based physical activity therapy by reducing both health-care cost and disease-related complications (61), which should be explored in future studies by combining HIIT with exercise goals beyond mere completion of the protocol.

To increase the societal relevance and impact of the current study protocol, two Parkinson patients who were consulted during the design process of this study expressed optimism about the procedures presented in this protocol. They also acknowledged the need for a better understanding of individual neural response patterns to different exercise intensities.

## Data Availability Statement

The original contributions presented in the study are included in the article/supplementary material, further inquiries can be directed to the corresponding author/s.

## Ethics Statement

The studies involving human participants were reviewed and approved by Medical Ethics Committee of Amsterdam UMC, Vrije Universiteit Medical Center (nr. 2029.083). The participants provided their written informed consent.
